### Dosing schedule

Both treatment arms follow the same dosing regimen. Hourly administration is maintained for 48 hours, followed by hourly administration while awake for five days, then two-hourly administration while awake for two additional weeks. Treatment discontinuation is considered if the ulcer heals, and adjustments are made if the ulcer resolves partially.

### Additional topical treatments

1. Fluorescein sodium ophthalmic strips: Used to highlight corneal epithelial defects (Tanzania: Contacare Ophthalmics and Diagnostics, India; Uganda: locally produced)
^
31
^.

2. Anaesthetic eye drops: Administered before procedures such as microbiology sampling. Proxymetacaine 0.5% eye drop Minims (Bausch and Lomb, UK).

3. Antibiotic eye drops: Used if bacterial/fungal mixed keratitis is suspected or for prophylaxis against secondary bacterial keratitis: Moxifloxacin 0.5% eye drops (Tanzania: Centaur Pharmaceuticals, India; Uganda: Abacus Parenteral Pharmaceuticals, Uganda)

4. Mydriatic eye drops: For pupil dilation to alleviate discomfort. Tanzania: Atropine 1% eye drops (Aurolab, India), twice daily; Uganda: Cyclopentolate 2% eye drops (Abacus Parenteral Pharmaceuticals, Uganda), three times a day.

5. Ocular hypotensive eye drops: Prescribed if intraocular pressure exceeds 25 mmHg. Usual first line treatment is timolol 0.5% eye drops (Tanzania: Allergan, India; Uganda: Abacus Parenteral Pharmaceuticals, Uganda).

### Ancillary treatment for refractory cases

Patients unresponsive to trial medication for seven days or more may receive additional treatments such as topical amphotericin B, oral ketoconazole, or intracameral amphotericin B, depending on ulcer depth and progression.

### Non-pharmacological treatment

Surgical interventions, performed by supervising consultant ophthalmologists, may include bandage contact lens insertion, tissue glue and patch application, or conjunctival flaps to manage small perforations or non-healing ulcers. Corneal transplant is not available in Uganda or Tanzania.

### Primary outcome measure

**
*Best Spectacle Corrected Visual Acuity (BSCVA) at Three Months:*
** Measured in logMAR units by a trial-certified optometrist, independent and masked to allocation. This outcome is selected for its functional significance and comparability with prior trials, including our recent Nepal trial
^
7,
16
^. Three months is chosen as it aligns with clinical experience indicating typical healing time for corneal ulcers. BSCVA will be assessed using an LED-backlit, Tumbling-E LogMAR chart under controlled conditions. Peek Acuity, a validated smartphone application, will be used if hospital visits are not feasible
^
32
^. LogMAR values for patients with CF vision or less will be applied, as previously described
^
33,
34
^.

### Secondary outcome measures

**Clinical Signs of Healing:** Including reduction of epithelial defect.
**Microbiological Culture Rates:** Assessing for positive or negative cultures.
**Other Clinical Outcome Measures:** Such as scar size or perforation rate.

### Outcome assessments

Participants will undergo reassessment at various intervals following enrolment, as outlined in
Table 3. Examinations will be conducted similarly to the baseline assessment. Adherence to treatment and symptoms, including side effects, will be queried and recorded at each follow-up. Trial medication adherence will be monitored by weighing eye drop bottles at specified follow-ups, with resupply provided as necessary. Visual acuity will be measured at each visit, with BSCVA assessed at the three-month follow-up (primary outcome measure). Quality of life questionnaires will be repeated at the final three-month follow-up. Slit-lamp examination and corneal photography will be performed at each visit. In vivo confocal microscopy will be repeated at specified intervals to assess fungal hyphae resolution. If the ulcer has not healed at the one-week follow-up, re-scraping for repeat culture will be conducted. Appointment cards will be provided for follow-ups, and transport costs will be covered for outpatient participants.

**Table 3. T3:** Baseline and follow-up assessment components.

Assessment Item	Baseline	Day 2	Day 7	Day 14	Day 21	Day 60	Day 90
History / Baseline questionnaire	X						
Check treatment adherence		X	X	X	X	X	X
Check for side effects		X	X	X	X	X	X
Visual Acuity – Presenting	X	X	X	X	X	X	X
Visual Acuity – BSCVA	X						X
Contrast Sensitivity	X						X
Slit-lamp Examination	X	X	X	X	X	X	X
Cornea Photography	X	X	X	X	X	X	X
*In vivo* confocal microscopy	X		X	X	X		
Cornea samples (Microbiology/PCR)	X		X				
Quality of Life Tools	X						X

### Treatment review

At each follow-up appointment, participants will be assessed by an ophthalmic clinician with expertise in fungal keratitis management. Clinical responses to antifungal treatments are generally slower compared to bacterial infections, often necessitating prolonged topical therapy for 4–6 weeks. As a result, adjustments to therapy are typically deferred for at least one week. Additional interventions may be required, including corneal glue application for perforations, conjunctival flap procedures, or therapeutic penetrating keratoplasty (corneal transplantation). 

### Stopping rules

If the study eye experiences a significant adverse event believed to be linked to the antifungal study medication, its use may be discontinued. The patient will then receive treatment as determined by the supervising ophthalmologist, without unblinding the randomisation code. Even if the study medication is stopped, the patient will continue scheduled follow-up visits. 

### Loss to follow-up

Low rates of loss to follow-up are anticipated based on prior clinical experience. Patients who miss follow-up visits will be contacted by phone, and reasons for non-attendance will be documented. Patients will be encouraged to attend for continued treatment and monitoring. If they are unable to visit the hospital due to illness or other barriers, home visits by the study team will be arranged. Reasons for loss to follow-up will be recorded and reported accordingly. 

### Data collection, management, confidentiality, and access to data

Data will be recorded on paper-based Clinical Record Forms (CRFs) securely stored at study sites. Scanned electronic copies will be saved daily on an encrypted drive, with backups made both on-site and off-site. Double data entry will be conducted into two separate MS Access databases, with data cleaning performed using EpiData version 3.1 (available for free at:
https://www.epidata.dk). Local study coordinators will supervise data collection and entry daily, and progress will be reviewed weekly by the study coordinator and the chief investigator at LSHTM. Data confidentiality will be maintained by restricting database access and securing paper documents in locked cabinets accessible only to authorised personnel. The database will require password authentication, with individual passwords assigned to data entry staff. Anonymised datasets will be used for further analysis. 

### Data and Safety Monitoring Board

The Data and Safety Monitoring Board (DSMB) for the trial comprises independent experts in bioethics, biostatistics, epidemiology, and ophthalmology, appointed by the Trial Steering Committee and approved by regulatory authorities. The DSMB convenes before the trial and periodically thereafter, with additional teleconferences as required. The DSMB oversees the study protocol, modifications, severe or unexpected events, and the interim analysis results, determining whether the trial should continue as planned or with adjustments. Ethics committee approvals from Tanzania, Uganda, and LSHTM are prerequisites, and all changes undergo DSMB review. 

### Monitoring for harm

Patients will be monitored for adverse events or reactions during each visit, using standardised definitions outlined in Appendix 2. Reporting protocols for adverse events, unexpected adverse reactions, and serious reactions will also follow Appendix 2. 

### Biological specimens

Procedures for processing and analyzing biological specimens are detailed in Appendix 3. 

### Sample size considerations

The study is designed to test the hypothesis that natamycin combined with chlorhexidine is superior to natamycin alone in improving the primary outcome (BSCVA at 3 months). Assuming a BSCVA of 0.5 logMAR in the natamycin-only group, a standard deviation of 0.62 in both groups, and an adjusted alpha of 0.0492 (to accommodate interim analysis using the O’Brien-Fleming method), a sample size of 304 ensures 80% power to detect a 0.2 logMAR improvement. Allowing for a 15% dropout rate, the total target enrollment is 358 participants across both sites. 

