### Eligibility criteria

Prospective participants must fulfil all the inclusion criteria while not meeting any of the exclusion criteria outlined in
Table 1. In essence, they should exhibit active fungal keratitis, defined as acute microbial keratitis characterised by corneal epithelial ulceration (>1mm in diameter), corneal stromal infiltrate, and signs of acute inflammation (e.g., conjunctival injection, anterior chamber inflammatory cells, hypopyon), alongside evidence of a filamentous fungal infection detected through smear microscopy and/or in vivo confocal microscopy (IVCM). IVCM has proven instrumental in identifying cases of fungal keratitis in our recent Nepal trial
^
16,
18
^, thereby contributing to robust evidence supporting its diagnostic utility in filamentary fungal keratitis. Previous studies have reported sensitivities ranging from 85.7% to 89.2% and specificities from 81.4% to 92.7%, respectively
^
22,
23
^. Given that some patients will be enrolled based on IVCM results, which may not reliably detect most bacteria, a subset of patients with microscopically confirmed fungal infection may subsequently manifest mixed infections upon study enrolment, as bacterial cultures may yield positive results a few days post-enrolment. As per our prior investigations, this scenario is anticipated to encompass approximately 10% of cases
^
16
^. These patients are included in the study but are excluded from the primary analysis of the primary outcome (as elaborated below). Secondary analyses will encompass mixed infections.

**Table 1. T1:** Inclusion and exclusion criteria for enrolment in Stage 1 (microbial keratitis cases) and Stage 2 (the randomised controlled trial).

Stage 1:	
Inclusion Criteria (all must be met):	Exclusion Criteria (any of the following):
1. Acute MK characterised by: • Corneal epithelial ulceration >1mm diameter • Corneal stromal infiltrate • Acute inflammation: e.g. conjunctival injection, anterior chamber inflammatory cells, hypopyon. 2. Adults (18 years and older) 3. Able to provide informed consent	1. Patients aged less than 18 years 2. Patients unable or unwilling to provide informed consent 3. Patients who do not have acute microbial keratitis or where there is a more likely alternative diagnosis
Stage 2:	
Inclusion Criteria (all must be met):	Exclusion Criteria (any of the following):

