### Analysis plan

An intention-to-treat (ITT) approach will be used, analyzing all data based on the assigned randomisation group, regardless of adherence to the treatment protocol. Analyses will follow CONSORT guidelines for non-inferiority trials
^
35
^, and a flowchart will summarize recruitment, randomisation, and follow-up by treatment arm. Baseline characteristics will also be summarized. Details of the SPIRIT checklist are provided as Extended Data and available online (see Data Availability Statement). 

**
*Primary outcome analysis – unadjusted*
**

The primary outcome (BSCVA at 3 months) will be analyzed using linear regression, including baseline BSCVA and treatment arm as covariates. Mixed fungal and bacterial infections identified at baseline will be excluded from the primary analysis. We will use our alpha of 0.0492 to test the null hypotheses at 0.0492 significance. Significance will be assessed using a two-tailed test at 0.0492 level for assessing superiority.

**
*Primary outcome analysis – adjusted*
**

If baseline covariate imbalances occur between treatment arms, adjusted analyses will be conducted to ensure treatment effects are not confounded by these differences. This is particularly important if natamycin + chlorhexidine has a better outcome than natamycin, as the adjusted treatment effects may account for this observed imbalance whilst the unadjusted analyses may not. Sensitivity analyses will allow us to show that any observed positive treatment effect is not solely explained by imbalances at baseline in any of the covariates.

**
*Secondary analyses of the primary outcome*
**

- Per-Protocol Analysis: Re-analysis will be conducted excluding participants with significant deviations, poor adherence (<50%), or mixed/non-fungal infections. 

- Mixed Infections: Secondary analyses will include mixed infections using the same methodology as the primary analysis. 

- Sensitivity Analyses: Missing data will be addressed through multiple imputation or non-random missing data models if necessary. Additional sensitivity analyses will assess outcomes in subgroups such as those with severe vision loss, corneal perforation, or therapeutic keratoplasty. 

**
*Analysis of other determinants for success*
**

Logistic regression models will identify factors associated with poor outcomes (BSCVA >1.0 logMAR), adjusting for trial arm. Multivariate models will refine predictors based on likelihood ratio tests. 

**
*Secondary outcome analysis*
**

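### The enrolment target of 358 allows for dropout but not for the mixed infections left out of the primary analysis: power on the plan's own inputs is about 76%, and the population is modified ITT, not ITT

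*Protocol article*

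**What the plan says.** All references are to the protocol article.

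- **Sample size considerations.** With an SD of 0.62 in each group and an alpha of 0.0492, "a sample size of 304 ensures 80% power to detect a 0.2 logMAR improvement". The section then adds one allowance: "Allowing for a 15% dropout rate, the total target enrollment is 358 participants across both sites".
- **Eligibility criteria.** Some patients enrolled on microscopy will prove to have a mixed infection when bacterial cultures are read a few days after enrolment, and "this scenario is anticipated to encompass approximately 10% of cases". These patients stay in the study but are left out of the primary analysis of the primary outcome.
- **Analysis plan, primary outcome analysis.** The exclusion is repeated: "Mixed fungal and bacterial infections identified at baseline will be excluded from the primary analysis". The test is fixed as follows: "Significance will be assessed using a two-tailed test at 0.0492 level for assessing superiority".
- **Analysis plan, opening paragraph.** The approach is named intention-to-treat, "analyzing all data based on the assigned randomisation group, regardless of adherence to the treatment protocol". The Methods part of the abstract also calls the primary analysis intention-to-treat.
- **Analysis plan, secondary analyses of the primary outcome.** Mixed infections come back in a secondary analysis that uses the primary method.
- **Analysis plan, reporting.** "Analyses will follow CONSORT guidelines for non-inferiority trials".

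**The concern.** The protocol predicts two separate losses between randomisation and the primary analysis, dropout and mixed infection, but the enrolment target is inflated for only one. If both occur as planned for, the primary analysis has fewer than the 304 patients on which the 80% figure rests. The stated power is then not what the design delivers.

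The analysis population is also described in two incompatible ways. An analysis of all data by assigned group cannot also leave out a foreseen tenth of randomised patients. A reader of the trial report would take the headline result to cover everyone randomised, which it would not.

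**Working it through.** **Inputs.** Difference 0.2 logMAR, SD 0.62 in both groups, alpha 0.0492, 80% power, 304 evaluable, 15% dropout and 358 enrolled come from the sample size section. The two-sided test comes from the analysis plan, 1:1 allocation from the randomisation section, and about 10% mixed infections from the eligibility section.

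**Step 1: reproduce the plan's figures.** With z = 1.9669 for two-sided 0.0492 and 0.8416 for 80% power:

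- n per arm = 2 × (1.9669 + 0.8416)² × 0.62² / 0.2² = 151.6, so 152 per arm and 304 in total (power 80.1%).
- 304 / 0.85 = 357.6, so 358.

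Both figures match. The 15% is used up by dropout, and nothing is left for another loss.

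**Step 2: apply both losses.** Taking dropout and mixed infection as independent:

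- Evaluable = 358 × 0.85 × 0.90 = 273.9, about 274.
- Standard error of the difference = 0.62 × √(4 / 273.9) = 0.0749.
- Power = Φ(0.2 / 0.0749 − 1.9669) = Φ(0.702) = 75.9% (75.6% with the noncentral t).
- Detectable difference at 80% power = 2.8085 × 0.0749 = 0.21 logMAR.

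If the two losses are added instead, 358 × 0.75 = 268.5 are evaluable and power is 75.0%.

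**Step 3: vary the two losses.** Power for 0.20 logMAR with 358 enrolled:

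| Dropout | Mixed infections | Evaluable | Power |
|---|---|---|---|
| 15% | 0% (as planned) | 304.3 | 80.1% |
| 15% | 5% | 289.1 | 78.1% |
| 15% | 10% | 273.9 | 75.9% |
| 15% | 15% | 258.7 | 73.5% |
| 10% | 10% | 290.0 | 78.2% |
| 5% | 10% | 306.1 | 80.4% |

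With 10% mixed infections, 304 evaluable patients remain only if dropout is at most 1 − 304 / (358 × 0.90) = 5.6%. Keeping 304 after both planned losses would take 304 / (0.85 × 0.90) = 397.4, so 398 enrolled.

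**Step 4: covariate adjustment.** The primary regression includes baseline BSCVA, while the sample size is that of an unadjusted comparison. Adjustment multiplies the residual variance by about 1 − r², where r is the correlation between baseline and three-month BSCVA. The loss is recovered when 1 − r² = 273.9 / 303.2, that is r ≈ 0.31. The protocol gives no r, so this is an assumption. At 274 evaluable, r = 0.2 gives 77.6%, r = 0.3 gives 79.7% and r = 0.4 gives 82.8%.

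**Step 5: the label.** The opening of the analysis plan and the abstract say intention-to-treat, the former on all data. The primary outcome paragraph and the eligibility section remove randomised patients. Both cannot describe the same analysis. The population actually defined is all randomised patients without a mixed infection identified at baseline, which is a modified ITT population.

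**The case against.** **Dropout may be low enough to absorb the exclusion.** The section on loss to follow-up expects low rates and plans phone contact and home visits. Transport costs are covered for outpatients, and a smartphone acuity test is available when a hospital visit is not feasible. At about 5% dropout the exclusion fits within 358. This stands as a limit on the size of the problem. It does not remove the problem, because the sample size section plans for 15%, calls it dropout and does not say that it covers exclusions.

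**The adjusted model may be more powerful than the sample size assumes.** This also stands. Without a stated correlation, neither a full recovery nor a definite failure to reach 80% can be claimed for the adjusted analysis.

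**The exclusion is disclosed, pre-specified and tied to baseline.** This stands too. A reader might infer that dropping patients after allocation biases the comparison, but the documents do not support that. The cultures are read late, but the samples are taken before trial treatment, so treatment cannot have affected who is excluded. A matching analysis that includes mixed infections is already planned.

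**The trial asks about fungal keratitis, so a fungal-only primary population is defensible.** Agreed. What needs correcting is the name and the power, not necessarily the population.

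**Conclusion.** The point holds as an inconsistency between sections. The figures 304 and 358 are correct for their inputs. What is missing is an allowance for an exclusion that the protocol itself predicts. On the plan's own inputs (15% dropout, 10% mixed infections, independent losses, no covariate gain) power is about 76% for 0.20 logMAR, roughly four points below the stated 80%. It ranges from 76% to 80% as dropout falls from 15% to about 5% with 10% mixed infections.

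A reader might infer that the trial is underpowered at 76% come what may. That goes too far, since the figure is conditional on full dropout and on no gain from baseline adjustment. Neither bias nor an inflated type I error is shown.

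The ITT label is wrong for the population defined. The non-inferiority reporting reference is a separate slip: the trial tests superiority throughout and states no margin. It has no bearing on power or on the exclusion, and it should not be read as a sign of a hidden non-inferiority aim.

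Overall this is a moderate issue: worth correcting, but not a threat to the trial's validity.

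**What to change.** 1. In the sample size section, state that the primary analysis is subject to both dropout and the exclusion of mixed infections, and give the power after both: about 76% for 0.20 logMAR, or 80% for 0.21, with about 274 evaluable. Add that this takes no credit for baseline adjustment and assumes the full 15% dropout.
2. In the abstract and the analysis plan, call the primary population modified ITT: all randomised patients analysed by assigned group, except those with a mixed infection identified from baseline samples.
3. Separately, replace the non-inferiority CONSORT reference with CONSORT for parallel-group superiority trials.

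These are wording changes and need no extra patients. The cost is a less favourable stated power.

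**Option, not a requirement.** Make the already planned analysis that includes mixed infections the primary one, and move the exclusion to the secondary list. That would give about 304 evaluable patients and earn the ITT label, subject to how missing outcomes are handled. Power would be about 80% only if the effect and SD are similar in mixed infections, for which the protocol gives no figures. It would also change the primary population of a trial listed as recruiting. It is therefore a protocol modification needing review, and it should be decided and documented without sight of unmasked outcome data.

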### Analysis plan

An intention-to-treat (ITT) approach will be used, analyzing all data based on the assigned randomisation group, regardless of adherence to the treatment protocol. Analyses will follow CONSORT guidelines for non-inferiority trials
^
35
^, and a flowchart will summarize recruitment, randomisation, and follow-up by treatment arm. Baseline characteristics will also be summarized. Details of the SPIRIT checklist are provided as Extended Data and available online (see Data Availability Statement). 

**
*Primary outcome analysis – unadjusted*
**

The primary outcome (BSCVA at 3 months) will be analyzed using linear regression, including baseline BSCVA and treatment arm as covariates. Mixed fungal and bacterial infections identified at baseline will be excluded from the primary analysis. We will use our alpha of 0.0492 to test the null hypotheses at 0.0492 significance. Significance will be assessed using a two-tailed test at 0.0492 level for assessing superiority.

**
*Primary outcome analysis – adjusted*
**

If baseline covariate imbalances occur between treatment arms, adjusted analyses will be conducted to ensure treatment effects are not confounded by these differences. This is particularly important if natamycin + chlorhexidine has a better outcome than natamycin, as the adjusted treatment effects may account for this observed imbalance whilst the unadjusted analyses may not. Sensitivity analyses will allow us to show that any observed positive treatment effect is not solely explained by imbalances at baseline in any of the covariates.

**
*Secondary analyses of the primary outcome*
**

- Per-Protocol Analysis: Re-analysis will be conducted excluding participants with significant deviations, poor adherence (<50%), or mixed/non-fungal infections. 

- Mixed Infections: Secondary analyses will include mixed infections using the same methodology as the primary analysis. 

- Sensitivity Analyses: Missing data will be addressed through multiple imputation or non-random missing data models if necessary. Additional sensitivity analyses will assess outcomes in subgroups such as those with severe vision loss, corneal perforation, or therapeutic keratoplasty. 

**
*Analysis of other determinants for success*
**

Logistic regression models will identify factors associated with poor outcomes (BSCVA >1.0 logMAR), adjusting for trial arm. Multivariate models will refine predictors based on likelihood ratio tests. 

**
*Secondary outcome analysis*
**

Secondary outcomes listed in
Table 4 will be analyzed using regression models appropriate for the data type, adjusting for any baseline imbalances. 

**Table 4. T4:** Secondary Outcome Measures that will be investigated as part of the trial, together with analysis details.

Secondary outcome measure	Details
Three-week BSCVA	We will analyze the secondary outcome of three-week Best Spectacle-Corrected Visual Acuity (BSCVA) in logMAR using the same methodology applied to the primary analysis of the primary outcome. The three-week BSCVA assessment will include values recorded between 18 days and 5 weeks, with the closest value to 3 weeks being selected.
Presenting VA by Peek	The presenting visual acuity (VA) assessed using Peek Acuity, with and without pinhole, will also be analyzed as a secondary outcome at three months. This measure will be particularly relevant if reliable BSCVA readings cannot be obtained at three months (e.g., if patients do not attend the clinic and at-home visual acuity testing is required). This analysis will follow the same approach as the primary analysis of the primary outcome. A sensitivity analysis, incorporating data from participants lost to follow-up, will use the most recent recorded observation of this variable.
Scar/infiltrate size at 1 week, 3 weeks and 3 months by slit lamp examination.	For scar or infiltrate dimensions, the geometric mean of the two principal axes (in mm) will serve as the outcome variable at one week, three weeks, and three months. The scar size, observed via slit lamp, will be compared between treatment groups at each time point using linear regression. This will include treatment arm and baseline infiltrate/scar size as predefined covariates, controlling for baseline differences.
Time to full epithelial healing (slit lamp examination by ophthalmic clinician)	The time to re-epithelialization will be calculated as the midpoint between the last review showing an epithelial defect (ED) and the subsequent review where no ED is observed. Fluorescein staining covering an area smaller than 0.5 mm will be considered indicative of a resolved ED, given the challenge of distinguishing smaller defects from pooling in healed areas. Time-to-healing analysis will utilize Cox proportional hazards regression, with treatment group as the primary predictor and baseline ED size (geometric mean in mm) included as a covariate. Survival curves for treatment groups will be plotted using Kaplan-Meier analysis up to the three-month endpoint. The proportional hazards assumption will be tested by stratifying baseline ED size into quartiles. If this assumption is not met, stratified results will be reported. Treatment failure (defined as an ED larger than 0.5 mm at the three-month review) will be compared between groups using Fisher’s exact test.
Rate of healing	The rate of ulcer size reduction will be evaluated by measuring changes in ED size over time intervals (1 week to 3 weeks, and 3 weeks to 3 months) and dividing by the number of days, producing a rate (mm/day). This will be analyzed using Cox regression.
Microbiological cure	For patients with persistent corneal ulcers (defined by ED presence) at day 7, a repeat corneal scrape and microbiological tests will be conducted. Microbiological cure at day 7 will be defined as the absence of growth on culture. Cure rates will be compared between treatment arms using logistic regression, adjusting for organism type (e.g., *Aspergillus spp.*, *Fusarium spp.*, or other).
Ulcer depth at 1 week and 3 weeks (slit lamp examination by ophthalmic clinician).	Depth of corneal ulcers (expressed as a percentage of healthy cornea thickness) will be compared between treatment groups at one week and three weeks. This analysis will adjust for baseline ulcer depth using linear regression.
Hypopyon height at 1 and 3 weeks, (slit lamp examination by ophthalmic clinician)	Hypopyon height (in mm) at one and three weeks will be compared between groups, adjusting for baseline height using linear regression.
Perforation and/or TPK and/or conjunctival advancement by three months (slit lamp examination by ophthalmic clinician)	The number of patients requiring perforation repair via Therapeutic Penetrating Keratoplasty (TPK), conjunctival advancement, or experiencing perforation itself by three months will be reported using confidence intervals and descriptive statistics. Since the study is not powered to detect significant differences in perforation or TPK rates, exploratory logistic regression analyses will estimate odds ratios for these outcomes between groups.
Loss of Eye	The proportion of patients requiring surgical removal of the eye (evisceration or enucleation) during follow-up will be described with confidence intervals. Logistic regression will explore treatment arm differences and associated risk factors.
Ocular adverse effects, slit lamp examination by ophthalmic clinician.	TThe occurrence of adverse events will be assessed by Fisher’s exact test. Poisson regression will compare adverse event rates, accounting for multiple events per participant.
Quality of life assessed using: EQ-5D, WHO/PBD-VF20, WHOQOL-BREF	QoL outcomes will be assessed using tools tailored to specific interests ^ 38 ^. Disease-related QoL will be evaluated with the WHO/PBD-VF20 (20-item Vision Function Questionnaire), which assesses the impact of visual impairment on mental well-being, dependency, and social functioning. For general health-related QoL, tools include the EQ-5D questionnaire, EQ-Visual Analogue Scale, and the WHOQOL-BREF. The EQ-5D provides standardized health outcome measures, while the WHOQOL-BREF evaluates four domains: Physical Health, Psychological Health, Social Relationships, and Environment. Scoring details for these tools are provided in Table 2. Comparisons of QoL scores between treatment groups will estimate the effects of chlorhexidine and natamycin. Adjustments will be made for variables like age, sex, socio-economic status, and recent health problems. Logistic, linear, and ordinal logistic regression methods will be employed depending on whether the outcome variables are binary, continuous, or ordered categorical. Mean scores and mean differences in QoL subscales and domains will be compared using t-tests and linear regression.
Cost effectiveness analysis, using EQ-5D data from 3 months and direct cost data	Direct costs incurred by patients will be collected at the three-month follow-up, with economic costs estimated from EQ-5D data collected at baseline and follow-up. Mean direct costs will be compared between treatment arms using t-tests. Changes in EQ-5D scores from baseline to follow-up will also be analyzed similarly.
Drug adherence	The rate of adherence to treatment protocols will be evaluated using descriptive statistics, comparing compliance between the two treatment arms.

**
*Interim analysis*
**

An independent statistician will conduct an interim analysis after 1/3 of participants complete follow-up. 

